**ASSESSMENTS**					
**Primary outcome measures**					
***Reactive balance control***—**Compensatory Step Execution tests during standing and walking** (single-step and multiple-step thresholds, first-step recovery initiation duration, first step duration, total balance recovery duration, total CoM displacement).			X		X

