### Primary Outcome Measures

Because this study deals with the ability to learn and generalize reactive balance responses that are acquired in a sitting position into a target context of fall risk factors and balance control performances in standing and walking situations, our primary outcome measures to evaluate the effect of PBBT during bicycle riding are derived from the ability to recover from unexpected external perturbations in the compensatory step execution tests during standing and walking. The best observational and kinematic measures to represent the reactive (compensatory) balance responses are: the single-step and multiple-step thresholds (observational parameters), and the first-step recovery initiation duration, first step duration, total balance recovery duration, and total CoM displacement (kinematic parameters) (14). All of these parameters have been previously found to be able to distinguish between younger and older adults (14) and fallers and non-fallers (15). The single-step threshold was previously shown to be an independent predictor of a future fall (16–21) and to reflect unsteadiness in reactive balance control among older adults with varying histories of falls (15). Moreover, excellent inter-observer reliability has been reported for single-step and multiple-step thresholds (ICC_2, 1_ = 0.978 and ICC_2, 1_ = 0.971, respectively; *p* < 0.001), and for first-step recovery initiation duration, first step duration, total balance recovery duration, and total CoM displacement (ICC_2, 1_=0.917, ICC_2, 1_=0.975, ICC_2, 1_=0.950, and ICC_2, 1_=0.918, respectively; *p* < 0.001) (14).

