#### Observational Analysis

We verify single-step and multiple-step threshold levels for AP and ML directions following a loss of balance using a Vicon Motion System (Oxford, UK), allowing image pauses, slow motion, and running of the image back and forth. The single-step threshold level is defined as the minimum perturbation magnitude that consistently elicited a single compensatory step for at least two consecutive perturbation magnitudes. The multiple-step threshold is defined as the minimum perturbation magnitude that consistently elicited a sequence of recovery steps. During the analysis, we explore the step recovery strategies during all single-step and multiple-step trials during the whole protocol.

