### Sample Size Estimation

Sample size requirements were calculated using PS power calculation software (66). Because the aim of the study is to examine the effect of perturbation-based bicycle training on various aspects of balance control, well-known parameters that reflect reactive, proactive, and standing postural balance control were selected. Calculations were performed separately to determine sample size requirements based on a single-step threshold in standing (reactive balance), voluntary step execution (i.e., foot contact time) (proactive balance), and ML postural sway (standing postural control), all reflective of unsteadiness in balance control between older and younger adults (13, 14, 50, 55, 58, 67, 68) and between fallers and non-fallers (13, 15–21, 55–58, 60). Type I error probability of 0.05 and Type II error probability of 0.2 was applied for the three two-sided test calculations. Based on our preliminary results, the compensatory single-step threshold in standing was 10.8 cm of lateral translation in older adults with bicycle riding habits compared to 7.9 cm in age- and gender-matched controls [data in processing], the ML postural sway in EO was 30.6 mm in older adults with bicycle riding habits compared to 38.8 mm in controls (31), and the step execution times (i.e., foot contact time) in single-task condition of older bicyclists were 104 ms less than those of the controls (921 vs. 1,025 ms) (30). Using net reduction values (2.9 cm, 8.2 mm, and 104 ms, respectively) in combination with the initial variance estimates (standard deviations of 3.45 cm, 7.8 mm, and 134 ms, respectively), it was determined that 27 participants per group would be required. To account for reported attrition rates of about 25% in studies involving older adults (69), we decided to include about 34 participants in each group for a total of 54 (27 × 1.25 = 34).

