### Statistical Analysis

PASW Statistics version 26.0 are used for statistical calculations. Baseline characteristics are compared using independent *t*-tests and Mann–Whitney *U*-tests for continuous and ordinal variables, respectively. Descriptive data analysis and tests for the assumptions of normality (Shapiro-Wilk's statistic) are followed by a two-way repeated measure analysis of variance (ANOVA) for within subjects (pre- vs. post-tests) and between groups (experimental vs. control groups). The primary outcome variables are the single-step and multiple-step thresholds, the first-step recovery initiation duration, first step duration, total balance recovery duration, and the MoS. These variables were previously found to be able to distinguish between younger and older adults (14) and between fallers and non-fallers (15). The single-step threshold was previously shown to be an independent predictor of a future fall (16–21) and to reflect unsteadiness in reactive balance control among older adults with varying histories of falls (15). The secondary laboratory outcome variables are foot contact time (voluntary stepping), and the ML CoP sway, as well as SDA parameters (Cd and Ds). All these parameters were previously found to reflect unsteadiness in balance control (13, 50, 55, 56, 58, 67, 68) related to falls (13, 55–58, 60), and also related to older adults who have bicycle riding habits (30). The other secondary outcome measures are the BBS, 6MWT, LLFDI, and FES-I. An intention to treat analysis is conducted by carrying the last obtained measurements forward for those participants who do not complete all aspects of the study. The significance level is *p* < 0.05.

The effect size (ES) (Hedge's g) between the two independent groups is calculated by dividing the difference between the means of each group by the pooled baseline standard deviation of both groups. Values between 0.2 and 0.49 are considered small, between 0.5 and 0.79 moderate, and 0.8 and higher is considered a large effect. In addition, for each outcome parameter, we explore whether a minimal detectable change has been reached. As data will be analyzed at the end of the study, there is no plan for interim analyses of primary and/or secondary variables.

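### The sixth primary outcome differs between sections, and six outcomes share primary status at one unadjusted 5% level with no lead outcome

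*Protocol article*

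**What the plan says.** Three places in the protocol article list the primary outcomes.

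- **Statistical Analysis:** "The primary outcome variables are the single-step and multiple-step thresholds, the first-step recovery initiation duration, first step duration, total balance recovery duration, and the MoS".
- **Primary Outcome Measures:** the same first five, but the list closes with "first step duration, total balance recovery duration, and total CoM displacement (kinematic parameters").
- **Table 1:** total CoM displacement is again the sixth entry. The measures are taken from "Compensatory Step Execution tests during standing and walking".

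Kinematic Analysis defines both candidates. MoS is the distance from the velocity-adjusted CoM position to the edge of the base of support. Total CoM path displacement is how far the CoM travels from before stepping until balance is fully recovered, and it is determined for multiple-step reactions.

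On direction, Observational Analysis says: "We verify single-step and multiple-step threshold levels for AP and ML directions". No such statement is made for the kinematic variables.

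On error rate, Statistical Analysis gives one line: "The significance level is *p* < 0.05". Sample Size Estimation says: "Type I error probability of 0.05 and Type II error probability of 0.2 was applied for the three two-sided test calculations". Those three calculations cover the single-step threshold in standing (a primary outcome), voluntary-step foot contact time and medio-lateral (ML) sway (both secondary).

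**The concern.** There are two separate problems.

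First, the list of primary outcomes is not fixed. CoM displacement and MoS are different quantities and may rest on different trials, since the former is tied to multiple-step reactions and the latter is not. The supporting text does not settle which is meant: both sections justify their own list by the same two cited studies on age and faller status. Primary Outcome Measures reports a reliability figure for CoM displacement (ICC 0.918), and the article gives none for MoS. As it stands, either could be presented as the prespecified primary outcome once results are known.

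Second, six variables are declared primary on equal terms, with one 5% level and no lead outcome. If any one significant result were read as a positive trial, the 5% error rate would not apply to that conclusion.

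**Working it through.** **1. The plan's own figure.** Inputs from Sample Size Estimation: two-sided alpha 0.05, power 80%, "Using net reduction values (2.9 cm, 8.2 mm, and 104 ms, respectively"), with standard deviations 3.45 cm, 7.8 mm and 134 ms. Formula: n per group = 2 × (1.960 + 0.842)² × (SD/difference)² = 15.70 × (SD/difference)².

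| Variable | Status | Calculation | n per group (noncentral t) |
|---|---|---|---|
| Single-step threshold, standing | primary | 15.70 × (3.45/2.9)² = 22.2 | 23 (24) |
| ML sway | secondary | 15.70 × (7.8/8.2)² = 14.2 | 15 (16) |
| Foot contact time | secondary | 15.70 × (134/104)² = 26.1 | 27 (28) |

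The stated 27 is reproduced. It is the largest of the three and is set by foot contact time. The threshold is the only primary outcome with planning figures, based on "the compensatory single-step threshold in standing was 10.8 cm of lateral translation" against 7.9 cm in controls.

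**2. Number of primary tests.** This depends on how the text is read.

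- 6: one test per variable (the minimum).
- 12: six variables × standing and walking.
- 16: two thresholds × two conditions × two directions = 8, plus four kinematic variables × two conditions = 8.
- 24: all six variables × two conditions × two directions. This is an upper reading, because analysis by direction is stated only for the thresholds.

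**3. Chance of at least one false positive at 0.05 each.** If independent, it is 1 − 0.95^m:

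- m = 6: 26.5%
- m = 12: 46.0%
- m = 16: 56.0%
- m = 24: 70.8%

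The document gives no correlation between outcomes, so a range is assumed. Simulated equicorrelated normal test statistics (400,000 draws for 6 and 12 tests, 200,000 for 24) give:

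| Correlation | 6 tests | 12 tests | 24 tests |
|---|---|---|---|
| 0.3 | 24.1% | 39.5% | 59.5% |
| 0.5 | 20.7% | 32.1% | 45.7% |
| 0.7 | 16.4% | 23.3% | 31.0% |
| 0.9 | 10.8% | 13.4% | 16.2% |

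Every entry exceeds 5%.

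**4. Effect of the two remedies on the single-step threshold.** With one primary outcome, alpha stays at 0.05, and power with 27 evaluable per group is 87% (86% by noncentral t). With six primary outcomes under Bonferroni, alpha is 0.05/6 = 0.00833, the need rises to 35 per group (37 by t), and power at 27 falls to 67% (64% by t).

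**The case against.** The article condenses a fuller protocol, and multiplicity rules are commonly left to an analysis plan that is not shown. That stands against criticising the absence of a correction or success rule as such. It does not remove what the article itself fixes: six equal primary outcomes, one level, and two conflicting versions of the sixth. A contradiction between sections is an error whatever a separate plan says.

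The independence figures also flatter the concern. Step initiation, first-step duration and total recovery duration are all timed from the same platform movement, so each later interval contains the earlier ones, and both thresholds come from the same ascending series. Strong correlation is plausible. This stands: the lower end of the range, about 11% for six tests, may be nearer the truth than 26%. It is still more than double 5%.

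A reader might infer four stronger things that the text does not support:

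- **That all six outcomes are tested in two directions, giving 24 tests and a 71% error rate.** The kinematic variables are not said to be analysed by direction.
- **That the trial will claim success on any one result.** No success rule is stated, and effect sizes and minimal detectable change are also planned.
- **That the trial is sized on the single-step threshold.** It is one of three sizing variables, and the 27 comes from foot contact time.
- **That defining MoS at any instant is itself an error.** That wording belongs to the general definition of the quantity; the analysis time point is a detail that can sit in the analysis plan.

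Finally, insisting on a single primary outcome is partly a preference. Holm or a fixed order across the six would also control the error rate.

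**Conclusion.** The point holds in two parts. The CoM displacement/MoS conflict rests on the text alone, needs no assumption, and must be resolved. The equal status of six primary outcomes at an unadjusted 5% level also stands: the familywise error is 26% under independence and about 24% to 11% at assumed equicorrelations of 0.3 to 0.9. It is larger if standing and walking are tested separately (46% for 12 tests if independent) or if the thresholds are also split by direction (56% for 16). These rates describe the chance of at least one significant primary result when there is no true effect on any of them. They matter for the trial's conclusion only so far as one such result would be taken as success.

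The power figures assume the plan's difference and standard deviation for the threshold, the two-group comparison used in its sample size calculation, and 27 evaluable per group.

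**What to change.** Before unblinding:

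1. Name one primary outcome: the single-step threshold in standing under lateral (ML) translation. It is the only primary outcome with planning figures, and Weaknesses states that the training perturbations are ML only.
2. Make the other five variables, and the walking and antero-posterior versions of the threshold, secondary. Alternatively, keep all six as primary and test them by Holm or in a stated fixed order.
3. Choose either total CoM displacement or MoS and enter it identically in Table 1, Primary Outcome Measures and Statistical Analysis.

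The cost is protocol wording and a matching registry entry (the registry record was not available for this review). With one primary outcome, the planned sample size need not change, but the other variables can no longer be called primary. The alternative keeps that label at some loss of power; the Bonferroni figures in the working indicate the loss at Holm's strictest step, while under a fixed order the loss falls on outcomes later in the sequence.

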**Secondary outcome measures**					
***Balance postural control***—**Postural stability test**(traditional CoP sway and SDA parameters)			X		X
***Proactive balance control***—**Voluntary step execution test** (Reaction Time, Foot Contact Time, Preparation Time, Swing Time)			X		X
***Clinical functional balance***—BBS			X		X
***Aerobic capacity***—6MWT			X		X
**Questionnaires**MMSE, LLFDI, FES-I			X		X
**Performance monitoring during training:** ° Balance recovery (Experimental PerTSBR only) ° Cognitive dual task ° Bicycle resistance				X	

*Overview of time assessments and outcome measures. Pre-study personal interview (-T1); Pre-intervention baseline assessment (T1), Assessment during each of the 24 training sessions during 12-week interventions (Training measurement), Post-test assessment (T2)*.

**Table 2 T2:** Details of the PerTSBR intervention training program–the intensity and the progression levels.

**Training session (number)**	**Platform tilting (deg)**	**Platform peak Vel. (deg/sec)**	**Platform peak Acc. (deg/sec^**2**^)**	**Type of training (blocked/random)**	**Type of perturbations (internal, external)**	**Type of external cues (none, visual, sensorimotor)**	**Number of perturbations per minute**	**Pedaling intensity (bicycle resistance)**	**Cognitive task type and difficulty**
1	0°	Hands-free cycling practice				None	0	0	None
2	2°	10	10	Blocked Lt	External only	None	4	0	None
3	3°	20	20	Blocked Rt	External only	Visual	4	1	None
4	4–5°	25	25	Blocked Rt-Lt	External only	Visual	4	1	None
5	5–7°	30	30	Blocked Rt-Lt	Internal & External	Visual	4	1	None
6	5–8°	30	30	Blocked Rt-Lt	Internal & External	Sensorimotor	4	1	None
7	6–9°	30	30	Random	Internal & External	Sensorimotor	5	1	Find the odd one out of 1
8	5–10°	30	30	Random	Internal & External	Sensorimotor	5	1	Find the odd one out of 2
9	7–11°	30	30	Random	Internal & External	Sensorimotor	5	2	Find the odd one out of 3
10	8–12°	30	30	Random	Internal & External	Sensorimotor	5	2	Find a specific object 1
11	5–13°	30	30	Random	Internal & External	Sensorimotor	5	2	Find a specific object 2
12	5–13°	30	30	Random	Internal & External	None	6	2	Find the differences 1
13	9–14°	30	30	Random	Internal & External	Sensorimotor	5	2	Find the differences 1
14	10–15°	30	30	Random	Internal & External	Sensorimotor	5	2	Find the differences 2
15	5–16°	30	30	Random	Internal & External	Sensorimotor	5	2	Find the differences 2
16	5–16°	30	30	Random	Internal & External	None	6	3	Find the differences 3

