### Data Collection and Outcome Measures

First, by personal interview with one of the researchers at the enrollment session (T1), each participant completes demographic, medical history, and past fall questionnaires (see Table 1). Then they undergo two assessment sessions: first at entry of the study (baseline assessment, T1), and the second at the end of the 12-week intervention period (T2). To ensure data quality, two research assessors blinded to group allocation and the training process receive training regarding data collection from the principal investigator and perform all measurements.

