### Weaknesses

In this study, we aim to improve balance control and balance reactive components by tilting perturbations. However, these tilting perturbations during bicycle riding may not be similar enough to balance loss situations that cause falls among older adults; thus, they may not be specific. Because of the lack of specificity in this model, we may find no effects of the intervention. Perturbations in the experimental group are limited to the ML direction only, while hip balance strategy, which is one target of this training method, are triggered mainly by anterior–posterior movements. Trainers are trained to follow the pedaling intensity according to the training program to control this endurance component in the two intervention groups, but although the bicycle resistance is set equally, it might be difficult to monitor the speed of pedaling for each participant. This program is less challenging than the PBBT in walking and standing, but it is still possible for older adults to have difficulties in hands-free riding or to progress very slowly in the training program, which may not be enough to lead to improvement. Lastly, since the PBBT is a challenging training approach, there is a risk that older adults will stop participating in the program (drop out). In regard to our RCT study, there are disadvantages (limitations) to the convenience sampling that may weaken this study. The convenience sampling can lead to the under-representation or over-representation of particular groups within the sample. For example, old volunteers that commits to train 3 months are different from the general population of older adults. This undermines our ability to generalize our results to the general population of older adults. However, in our RCT the participant is randomly allocated to two groups thus a significant improvement in balance control system in one of the groups may truly represent a change in the balance function.

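### Outcomes are measured only at T1 and T2, so carrying the last value forward enters anyone without a T2 measurement as exactly zero change

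*Protocol article*

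**What the plan says.** Under Statistical Analysis the protocol gives its only missing-data rule: "An intention to treat analysis is conducted by carrying the last obtained measurements forward for those participants who do not complete all aspects". The model is a "two-way repeated measure analysis of variance (ANOVA) for within subjects (pre- vs. post-tests) and between groups (experimental vs. control groups").

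Data Collection and Outcome Measures fixes two outcome assessments: "first at entry of the study (baseline assessment, T1), and the second at the end of the 12-week intervention period (T2"). Table 1 places every primary and secondary outcome at those two points. Its third measurement column, described in the table note as "Assessment during each of the 24 training sessions during 12-week interventions (Training measurement), Post-test assessment (T2"), holds training monitoring: balance recovery (experimental arm only), the cognitive task and bicycle resistance. None of these is a trial outcome.

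Three other statements bear on the point. Sample Size Estimation allows for attrition of about 25%. Informed Consent says participants are told that improvement is expected in either group. Weaknesses says of the challenging perturbation approach that "there is a risk that older adults will stop participating in the program (drop out").

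**The concern.** Carrying a value forward presupposes an intermediate value. Here there is none between baseline and the end of training, so the rule amounts to baseline carried forward. A missing T2 becomes a change of zero, and the analysis treats it like a measured result.

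Three things are at stake.

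- **Estimate.** It can be pulled toward zero. If loss of T2 differs by arm while both arms improve, it can also be shifted in either direction for reasons unrelated to treatment.
- **Standard error.** It is computed as if all 34 per arm had been measured, with no allowance for not knowing the missing values.
- **Label.** The result is presented as intention to treat, although keeping everyone in the denominator does not make the filled-in values right.

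The rule is worded for the analysis as a whole, so it reaches every primary and secondary outcome.

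**Working it through.** **Inputs from Sample Size Estimation.** Differences 2.9 cm, 8.2 mm and 104 ms; SDs 3.45 cm, 7.8 mm and 134 ms; two-sided 5% level; 80% power; 27 per group, raised to 34; attrition about 25%.

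**Plan's own figure.** n per group = 2 × (1.960 + 0.842)² × (SD/difference)².

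- Step threshold: 22.2, so 23.
- ML sway: 14.2, so 15.
- Foot contact time: 26.1, so 27.

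The largest is the stated 27, and 27 × 1.25 = 33.75 gives the stated 34. The inputs are therefore read correctly. In SD units the threshold effect is 2.9/3.45 = 0.84.

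**What the rule does.** With two time points, the group-by-time test in the repeated-measures ANOVA is equivalent to a t-test on change. Without T2, change = T1 − T1 = 0. Let pE and pC be the proportions without T2, c the gain shared by both arms and d the true extra effect. If those without T2 would have responded like the others, then

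expected estimate = (1 − pE)(d + c) − (1 − pC)c.

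**Equal loss, 25% in each arm.** The shared gain cancels, leaving 0.75d:

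- 0.75 × 2.9 = 2.18 cm
- 0.75 × 8.2 = 6.15 mm
- 0.75 × 104 = 78 ms

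At the loss that 34 per arm actually allows, 7/34 = 20.6%, 2.9 cm becomes 2.30 cm.

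**Unequal loss (35% experimental, 15% control; assumed).**

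- d = 0.84 SD, c = 0.5 SD: 0.65 × 1.34 − 0.85 × 0.5 = 0.446 SD.
- d = 2.9 cm with a control gain of 0, 1 or 2 cm: 1.89, 1.69 or 1.49 cm.
- Split reversed, same control gains: 2.46, 2.67 or 2.87 cm.
- d = 0: the estimate is −0.20c, which is −0.10 SD at c = 0.5 and −0.16 SD at c = 0.8. This runs against the experimental arm; reversing the split reverses the sign.

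**Simulation.** 34 per arm, pre-post correlation 0.5 (assumed), loss of T2 unrelated to outcome. Separate runs differ by a point or two.

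| Scenario | Carry-forward | Change scores, observed T2 | Observed T2, baseline-adjusted |
|---|---|---|---|
| d = 0.84, c = 0.5, 25%/25% | 0.63 SD, power about 75% | 0.84 SD, 82–84% | 0.84 SD, about 92% |
| d = 0.84, c = 0.5, 35%/15% | 0.45 SD, power about 45% | 0.84 SD, about 83% | 0.84 SD, about 91% |
| d = 0, c = 0.5, 35%/15% | −0.10 SD, rejection about 7% | about 5% | about 5% |
| d = 0, c = 0.8, 35%/15% | −0.16 SD, rejection about 10–12% | about 5% | about 5% |
| d = 0, c = 0.5, 25%/25% | 0, rejection about 5% | about 5% | about 5% |

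**Opposite assumption.** If those without T2 truly gained nothing, the all-randomised effect at 25% loss is 0.75 × 0.84 = 0.63 SD. Carry-forward then returns 0.63 SD without bias, and the observed-data analyses overstate it at about 0.84 SD.

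**The case against.** The strongest reply is that the size of the bias, and even its presence, depends on outcomes nobody will see. People who leave early may gain little. For an effect under actual adherence, zero change could then be close to right and the completers' estimate too large. This stands: the shrinkage is conditional, and the alternatives rest on a missing-at-random assumption that cannot be tested either. It does not justify fixing the answer at zero for everyone without T2 when the protocol itself expects both arms to improve.

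Stronger readings that a reader might infer, and why the documents do not support them:

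- **Every dropout is scored as no change.** Only those without T2 are. Nothing in the protocol makes T2 conditional on attendance at training.
- **Dropout will differ by arm.** Weaknesses names only a risk. Data Monitoring reports similar adverse events in the perturbation and control groups of earlier studies, and training difficulty is adapted to the trainee. The 35%/15% split is illustrative.
- **Power falls from 91% to 45% because of the rule.** Part of that gap is baseline adjustment. Like for like, on change scores, the comparison is 83% with 45%, or 82–84% with 75% at equal loss.
- **False positives favour the new training.** With equal loss the error rate stays near 5%. In the illustrated split the spurious difference runs against the experimental arm.
- **Carry-forward is the declared primary analysis.** The protocol sets no hierarchy. Powering on 27 and inflating for attrition would also fit a completers' analysis. Still, carry-forward is the only missing-data method it states.

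A statistical analysis plan might add detail, but this is a rule the protocol states, not a gap left for later.

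**Conclusion.** The point holds for participants without a T2 measurement. For them the rule is baseline carried forward, and the imputed zeros are analysed as data.

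That the imputed change is exactly zero follows from the visit schedule and needs no assumption. The size of the bias does need assumptions. If those without T2 would have responded like completers, 25% loss in each arm removes a quarter of any true effect and costs roughly 7 to 9 points of power (correlation 0.5, shared gain 0.5 SD). If they gained nothing, the shrinkage bias is nil. Under the illustrative unequal split the estimate roughly halves. With no true effect and a shared gain of 0.5 to 0.8 SD, the error rate rises to about 7–12%. The documents give no dropout rates by arm, shared gain or pre-post correlation, so those figures show a range and are not forecasts.

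The rule should be replaced before the outcome data are analysed.

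**What to change.** In Statistical Analysis, replace the carry-forward sentence with the following elements:

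1. The already planned T2 assessment is attempted for everyone randomised, whatever their training attendance.
2. Participants are analysed in the arm to which they were allocated, using a baseline-adjusted model of observed T2 or a baseline-constrained mixed model. Multiple imputation by arm from T1, age and attendance is an acceptable alternative.
3. The missing-at-random assumption is stated.
4. Two sensitivity analyses are named: baseline carried forward, and one in which participants without T2 do worse than comparable completers.

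With a single post-baseline visit, a mixed model recovers little from people who have no T2, so the first element matters most.

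The cost is a change of wording and a little more programming, with no added participants or planned visits. The drawback is reliance on an untestable assumption, which the sensitivity analyses are there to probe.
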